### Intervention

For these patients, a standard lateral cephalometry (the ORTHOPHOS brand device, which has a voltage of 200 to 240 volts and takes images with an output of 230 volts) is prepared before the operation, and the points and angles of the study will be analyzed using a gauge and a calibrated protractor [5, 10, 13, 14]. On the day of the operation, two sets of surgery are prepared according to the two types of study interventions, and at that time, the corresponding envelope is opened according to the order of referral and the patient’s assigned code, and the type of intervention is determined. We have 2 groups: the control group will not have any ANS reduction, and the test group will have ANS reduction. For patients undergoing surgery, after the patient is anesthetized by the anesthesia service, the routine preparation and the necessary injections will be performed in the surgical areas. Then, we will start the incision with the surgical blade no. 15 in the depth of the buccal vestibule of the upper jaw from the alignment of upper right first molar (16) to upper left first molar (26), the flap is pushed aside, and the periosteum will be separated from the bone in order to have the access to the bone for LeFort I incision. Then, the osteotomy lines are drawn and cut with a saw, and the maxilla will be separated from the base of the nose after the down fracture; then, the maxilla is placed in a new and appropriate position (advancement 3–5 mm) and by two “L” plates with 4 holes, and two straight plates with 4 holes will be fixed. If there is a need for ANS reduction, the ANS is completely removed by a large-sized round carbide bur. The surgical process continues, and after the surgery, we will follow-up the patient for 3 months, and after 3 months, we will request a post-op radiography to collect final data [15].

The second lateral cephalometry will be requested from the same radiology center in the same position as the previous one. The desired data for the research work will be measured by the same person with the same equipment; it should be noted that all the cephalometric measurements (the baseline and follow-up radiographs) will be measured twice, and the average is recorded as the desired number of that variable; then, the obtained results will be subjected to statistical analysis (Fig. 1). The patients will be excluded from the trial if they get pregnant, leave their orthodontic treatment half-finished, or leave the study at their own will.

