## Allocation and randomization

### Randomization

Every participant will receive a unique numerical code, which will be enclosed within a securely sealed envelope. The envelopes will remain unopened until the procedure is conducted by external investigators. As a result, the participants will be divided into two groups: group 1 (with ANS reduction) and group 2 (without ANS reduction). An independent investigator will utilize a web-based randomization service available at www.randomization.com to generate a randomized sequence. The envelopes are opened during the surgery by surgical assistant. Until that moment, the result of the allocation process in each sample is not known.

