### Statistical analysis

To assess the consistency of descriptive data, Cohen’s *k* statistic will be employed. Descriptive statistics, such as frequency counts (both absolute and relative) and metric data (such as arithmetic mean, standard deviation, and median), serve as examples of the types of statistics used. The consistency between the two examiners for continuous data, such as clinical parameters, will be assessed using the intraclass correlation coefficient. Enumerated data will be presented as percentages, while measured data will be reported as mean standard deviation or median (quartile spacing). We will assess the effects of differences in measurement time between the two study groups at baseline and follow-up by conducting an analysis of variance (ANOVA), considering the type of intervention as a factor. All statistical analyses will be conducted using SPSS 25.0. The significance threshold is set at 0.05.

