### Missing data

When determining the sample size for the examination, the potential for participants to become untraceable is considered and factored into the calculations. Furthermore, any missing data (such as loss to follow-up, death, withdrawal, etc.) will be addressed using the multiple imputations approach to ensure completeness.

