## Ethical consideration

### Ethical approval

The recruitment and treatment procedures for this study were approved by the Research Ethics Committees, Islamic Azad University-Dental Branch, Tehran, Iran (IR.IAU.DENTAL.REC.1400.035). Eligible participants will receive detailed information about the trial’s consent requirements. Individuals who do not provide consent will not be included in the final analysis.

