### Withdrawal

All patients will be given all the information they need about the study before any treatment begins. Patients can leave the study at any time for any reason. All patients will receive the best care possible, whether or not they participate in the study.

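### Patients who leave, become pregnant or stop orthodontics are excluded from the trial, even after allocation, while withdrawals are also to be imputed: the two sections need reconciling

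*Protocol article*

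**What the plan says.** The Intervention section ends its description of follow-up with a rule on leaving: "The patients will be excluded from the trial if they get pregnant, leave their orthodontic treatment half-finished", "or leave the study at their own will". The rule is separate from the entry criteria and carries no time limit.

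The Missing data section says that "any missing data (such as loss to follow-up, death, withdrawal, etc.) will be addressed using the multiple imputations approach". The Withdrawal section confirms that "Patients can leave the study at any time for any reason", so a withdrawal is foreseeable.

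On timing, the Randomization section states that "The envelopes are opened during the surgery by surgical assistant", and the Intervention section that "after the surgery, we will follow-up the patient for 3 months", with the second radiograph at the end of that period.

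The Statistical analysis section plans "conducting an analysis of variance (ANOVA), considering the type of intervention as a factor" without naming the patients who enter it. The only explicit statement about who is left out of the analysis is under Ethical approval: "Individuals who do not provide consent will not be included in the final analysis". That does not cover a consented, randomised patient who later leaves.

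**The concern.** Allocation becomes known at surgery and the endpoint is read three months later, so the exclusion rule reaches patients who are already randomised and operated on.

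Two things follow. First, for a patient who withdraws, one section can be read as removing the patient and another as keeping the patient with an imputed value. If that is left open, the choice can be made after outcomes have been seen. Second, a patient who stops orthodontics may still be able to have the three-month cephalogram. Read literally, the rule discards that patient even though nasolabial angle and upper lip length could be measured.

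Leaving may be related to the result. The Discussion says that soft tissue appearance is the main motive for most patients, and patients can see their own profile. Challenges and limitations mentions a possible sub-nasal depression from excessive ANS removal, which is a visible effect tied to one arm. With 13 patients per arm, each exclusion is 1/13 = 7.7% of an arm.

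**Working it through.** **1. The sections side by side**

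| Event after allocation | Intervention | Missing data | Status |
|---|---|---|---|
| Voluntary withdrawal | excluded from the trial | named, imputed | conflict if exclusion covers the analysis |
| Unfinished orthodontics | excluded from the trial | not named | exclusion after randomisation; endpoint may be obtainable |
| Pregnancy | excluded from the trial | not named | exclusion after randomisation |

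Only the first row is named in both sections. The other two could come under Missing data only through its closing et cetera.

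**2. The plan's own sample size**

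Inputs from Sample size: between-group effect size f = 0.6, 13 per group. Alpha is 0.05 (Statistical analysis). Beta is read as 0.2, although the sentence is unclear. For a two-group F test:

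- noncentrality λ = N × f², degrees of freedom 1 and N − 2
- equivalent standardised difference d = 2f = 1.2

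With N = 26: λ = 26 × 0.36 = 9.36, critical F(1, 24) = 4.26, power 0.835. The smallest n reaching 0.80 is 12 per group (λ = 8.64, power 0.802). The stated 13 is therefore reproduced to within one patient per group.

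**3. Precision lost (the number excluded is an assumption)**

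| Analysed | λ | Power |
|---|---|---|
| 13 + 13 | 9.36 | 0.835 |
| 12 + 12 | 8.64 | 0.802 |
| 12 + 11 | 8.26 | 0.783 |
| 11 + 11 | 7.92 | 0.763 |
| 10 + 10 | 7.20 | 0.718 |

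For 12 + 11, λ = d² × n₁n₂/N = 1.44 × 132/23 = 8.26. Three exclusions take power below 0.80. Missing data says that losses were allowed for, but the target of 26 is exactly twice the stated minimum of 13 and no rate is given.

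**4. Selection bias (assumed: 2 of 13 lost from one arm, the other arm intact, no true difference, normal data)**

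The tendency to leave is given correlation r with the outcome, the two patients with the strongest tendency leave, and a two-sided t test at 0.05 is run on 11 against 13 patients. The expected shift of the arm mean is r × 0.257 SD.

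| Relation of leaving to outcome | Shift of arm mean | False-positive rate (simulated) |
|---|---|---|
| r = 0 | 0 | about 5% |
| r = 0.3 | 0.08 SD | 5.5% |
| r = 0.5 | 0.13 SD | about 6% |
| r = 1 (two highest values always leave) | 0.26 SD | about 11% |

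The last row needs perfect selection from one tail in one arm only.

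**The case against.** The strongest reply is that exclusion from the trial only ends participation. The rule stands at the end of the follow-up description, and where the article means the analysis it says so, under Ethical approval. On that reading a patient leaves and the missing endpoint is imputed, so both sections can be followed. This reading is possible and the conflict is conditional on its being wrong. But the article does not state it, and it does not explain what happens to an obtainable cephalogram from a patient who stopped orthodontics.

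A reader might infer that all three events are subject to contradictory rules. The text does not support that: only withdrawal is named in both places.

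The rule also covers events before surgery. Those occur before allocation is known and do not bias the comparison.

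Patients are blinded to allocation (Blinding), both arms have the same 3–5 mm advancement, and follow-up is short. The documents give no withdrawal rate and no evidence that leaving depends on arm. This lowers the risk; it does not remove it, because the result is visible to the patient.

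On power, imputation does not in general restore information that was never collected. The rule itself costs power only where a cephalogram could still have been obtained.

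It might also be said that the analysis set belongs in an unseen analysis plan. Its absence from the article would be no finding. A stated exclusion rule that reaches randomised patients is one.

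**Conclusion.** The point holds in this form. The Intervention and Missing data sections conflict on voluntary withdrawal unless exclusion from the trial is meant only as the end of participation. For pregnancy and unfinished orthodontics, the literal rule departs from analysis as randomised and can discard an observable endpoint.

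The consequence is a risk. With two patients lost from one arm, the false-positive rate lies between about 5% and about 11%, and near 6% under moderate selection. A reader might take the upper figure to mean that the error rate is doubled; that holds only in the worst case. At the planned effect, power falls from 0.835 to 0.763 if two patients per arm are excluded. The number excluded and the strength of selection are assumptions, since the documents give neither.

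**What to change.** Reconcile the Intervention and Missing data sections with text such as:

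*Pregnancy, stopping orthodontic treatment or leaving the study may end a patient's participation but does not remove a randomised patient from the analysis. All randomised patients are analysed in the arm to which they were allocated. Any three-month cephalogram that is available with the patient's consent is used; otherwise the outcome is treated as missing and imputed as described under Missing data. Any analysis that leaves these patients out is a sensitivity analysis only.*

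Whether a radiograph is taken in a pregnant patient is a clinical decision that this change does not address. The cost is a few sentences of protocol wording, with no extra patients or visits.

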### Outcomes

An oral and maxillofacial radiologist will assess the nasolabial angle and upper lip length using a lateral cephalometry before the surgery. Three months following surgery, a second lateral cephalometry will be performed. With the same basic evaluation methods, nasolabial angle and upper lip length will be assessed.

### Sample size

According to the results of the study by Mahsoub R, et al., using the Advanced Repeated Measures Anova Power Analysis option of the Pass11 software, considering *α* and *β* = 0.05 for both within-between subject variables equal to 0.2, the repeated factor with two repetitions and the effect size equal to 0.5 and the two-way between subject factor with an effect size equal to 0.6, the minimum sample size required for each of the two study groups was calculated as 13 samples [16].

### Data collection and management

All participants will be allocated an individual trial identification number during the study. Data collection is limited to authorized members of the research team. These team members are required to maintain confidentiality and utilize the data solely for scientific purposes. The information is securely stored both electronically and in hard copy format. Investigators are provided with unique login credentials to access the data on the secure platform, ensuring privacy. To prevent bias, an independent investigator will perform the statistical analysis.

### Training and calibration

The surgical process will be performed by one specialist ([name]) with over 15 years of professional working experience. He is also an expert in the field of orthognathic surgery. An independent investigator will do the measurements before the surgery and after that. The research team consists of an oral and maxillofacial surgery resident and a final-year dental student, both of whom have a minimum of 4 years of clinical experience and have received training in accuracy and reproducibility to ensure compliance. A certified researcher with extensive years of expertise will be responsible for collecting clinical data, patient testimonials, and information on complications to maintain consistency.

### Statistical analysis

To assess the consistency of descriptive data, Cohen’s *k* statistic will be employed. Descriptive statistics, such as frequency counts (both absolute and relative) and metric data (such as arithmetic mean, standard deviation, and median), serve as examples of the types of statistics used. The consistency between the two examiners for continuous data, such as clinical parameters, will be assessed using the intraclass correlation coefficient. Enumerated data will be presented as percentages, while measured data will be reported as mean standard deviation or median (quartile spacing). We will assess the effects of differences in measurement time between the two study groups at baseline and follow-up by conducting an analysis of variance (ANOVA), considering the type of intervention as a factor. All statistical analyses will be conducted using SPSS 25.0. The significance threshold is set at 0.05.

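### The planned ANOVA does not use the pre-operative value as a covariate; it is valid, but ANCOVA would usually be more precise at the cost of one degree of freedom

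*Protocol article*

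**What the plan says.** The Statistical analysis section of the protocol article gives the model in one sentence. It begins "We will assess the effects of differences in measurement time between the two study groups at baseline and follow-up" and ends "by conducting an analysis of variance (ANOVA), considering the type of intervention as a factor". The error rate follows: "The significance threshold is set at 0.05". No covariate is named there or elsewhere in the article.

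Three other sections help to read that sentence:

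- Objective and hypothesis states the null hypothesis on the changes in nasolabial angle and upper lip length.
- Outcomes gives each patient one value before surgery and one at three months: "An oral and maxillofacial radiologist will assess the nasolabial angle and upper lip length using a lateral cephalometry before the surgery", with a second film after three months assessed in the same way.
- Sample size arrives at 13 per group "using the Advanced Repeated Measures Anova Power Analysis option of the Pass11 software". Time enters as a within-patient factor with two levels and an assumed effect of 0.5; for the groups, the section takes "the two-way between subject factor with an effect size equal to 0.6".

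**The concern.** The best predictor of a patient's 3-month nasolabial angle or lip length is likely to be the same measurement before surgery. That value is collected for everyone, yet the model uses it only as one of two measurement times. A change-score comparison subtracts the whole baseline value whatever the correlation between the two films. ANCOVA estimates how much of it to subtract. When the correlation is well below 1, subtracting all of it adds noise.

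With 26 patients this matters, because chance differences between arms at baseline can be sizeable: the standard deviation of the baseline mean difference is √(2/13) = 0.39 SD units.

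A second weakness is that the sentence does not say which ANOVA term answers the hypothesis. In a repeated-measures ANOVA the time-by-group interaction and the group main effect are different tests with very different power.

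**Working it through.** **Inputs from the protocol article.** Sample size: 13 per group, between-group effect size 0.6. Beta 0.2 is taken from a garbled sentence ("for both within-between subject variables equal to 0.2"). Statistical analysis: alpha 0.05.

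**Assumptions.** Two-sided test. The 0.6 is Cohen's f, so for two groups d = 2 × 0.6 = 1.2. This is applied as a 3-month difference of 1.2 SD of the outcome, with equal SDs at both times. The pre-post correlation ρ is not given, so a range is shown.

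**The plan's own figure.** Two-group F test with 1 and N − 2 df and noncentrality N × f². At 12 per group: 24 × 0.36 = 8.64, power 80.2%. At 13 per group: 26 × 0.36 = 9.36, power 83.5%. The minimum by this route is 12, so the stated 13 is reproduced to within one patient per group.

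**Variance of the group difference**, in units of σ² × 2/13:

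- change score, or time-by-group interaction: 2(1 − ρ), 24 error df
- ANCOVA: (1 − ρ²) × (1 + 1/(N − 4)) = (1 − ρ²) × 1.045, 23 error df. The second factor is the small-sample price of estimating the slope.

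| ρ | change | ANCOVA | ratio |
|---|---|---|---|
| 0.3 | 1.40 | 0.951 | 0.68 |
| 0.5 | 1.00 | 0.784 | 0.78 |
| 0.7 | 0.60 | 0.533 | 0.89 |
| 0.8 | 0.40 | 0.376 | 0.94 |
| 0.9 | 0.20 | 0.199 | 0.99 |
| 0.95 | 0.10 | 0.102 | 1.02 |

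**Power at a 3-month difference of 1.2 SD**, by noncentral t with noncentrality 1.2/√(variance × 2/13). For example, at ρ = 0.3 it is 1.2/√(1.40 × 0.1538) = 2.59 for change and 1.2/√(0.951 × 0.1538) = 3.14 for ANCOVA.

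| ρ | change / interaction | ANCOVA | group main effect |
|---|---|---|---|
| 0.3 | 70% | 85% | 44.5% |
| 0.5 | 84% | 91% | 40% |
| 0.7 | 97% | 98% | 36% |

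The group main effect compares the mean of the two measurements. Surgery cannot affect the pre-operative one, so the difference is halved to 0.6 SD, while the variance is (1 + ρ)/2. The noncentrality at ρ = 0.5 is 0.6/√(0.75 × 0.1538) = 1.77.

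**A second calibration.** If the 1.2 is instead taken in SDs of the change score, change-score power is 83.5% at every ρ. ANCOVA then has 94.4%, 91.1%, 87.4%, 85.5% and 83.6% at ρ = 0.3, 0.5, 0.7, 0.8 and 0.9. The pattern is the same.

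**Validity.** In 20,000 simulated trials at each of ρ = 0.3, 0.5, 0.7 and 0.9, with no true effect, the type I error of change score, follow-up-only, main-effect and ANCOVA tests was between 0.048 and 0.051.

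**The case against.** The strongest reply is that the plan hangs together. The hypothesis concerns changes, the sample size uses a repeated factor with two levels, and the analysis sentence speaks of measurement times compared between groups. That describes a time-by-group test, which is unbiased under randomisation and holds its error rate. This stands: ANCOVA is a refinement, and nothing in the planned test is wrong.

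The reply continues that the gain rests on an unknown correlation, which could be high. The Intervention section has one person measure all films with the same equipment, each film twice and averaged. At ρ = 0.9 ANCOVA gains almost nothing, and at 0.95 it is about 2% worse. This also stands, and ANCOVA cannot be said to have the smallest variance everywhere or to be free.

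Three stronger readings are tempting but are not supported:

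- *Baseline is ignored.* It is used as a repeated measurement. A follow-up-only comparison, with 84% power at any ρ in the first calibration, is not the natural reading. ANCOVA would not beat it anyway at ρ of about 0.2 or below.
- *The group main effect is the planned test.* The sentence does not exclude it, but the hypothesis and the reference to measurement times point to the interaction. The 36-45% shows the risk of leaving the term unnamed; it is not the expected power.
- *A separate significance test at baseline is planned.* The wording more naturally names the two measurement times.

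Finally, covariates are often left to an analysis plan, and this is a condensed article. But the article does state a method, ANOVA with intervention as the factor, so the point concerns a stated choice.

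**Conclusion.** The point holds as one of efficiency. The planned analysis, read as a time-by-group test, is valid but usually less precise than ANCOVA. The variance falls by about 32% at a correlation of 0.3, 22% at 0.5, 11% at 0.7 and 6% at 0.8, and by almost nothing at 0.9. In power terms the gain is material at the low end (70% to 85%) and about one point at 0.7 (97% to 98%).

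These figures rest on 13 analysed patients per arm, equal SDs before and after surgery, 0.6 read as Cohen's f, and a correlation that the article does not give. Against the change score, ANCOVA is better or essentially tied over the whole range shown, and nobody knows the correlation in advance. That makes it the safer choice for a trial of 26 patients.

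The unnamed test term is a related defect that the same sentence would cure. A reader might infer bias or an invalid test from the missing covariate; the calculations show neither.

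**What to change.** Replace the ANOVA sentence in Statistical analysis with, for example: *For each outcome, the 3-month value will be compared between groups by ANCOVA with the pre-operative value of the same outcome as covariate. The adjusted mean difference (degrees or mm) with its 95% confidence interval will be reported.* Use the same model within the multiple imputation described under Missing data.

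The hypothesis on changes need not be reworded: with baseline as covariate, ANCOVA on the change and ANCOVA on the 3-month value give the same treatment estimate. Naming this model also settles which term is the test.

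The cost is one sentence and one error degree of freedom (23 instead of 24). No further data or patients are needed, and the stated SPSS package can fit the model. The downside is little or no gain if the correlation is about 0.9 or higher. The change should be made before anyone sees outcomes by group.

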**Method and design:**

This study is designed as a randomized controlled trial. A total of 26 class III skeletal patients with maxillofacial abnormalities will be recruited from the maxillofacial clinic of Bu-Ali and Farahikhtegan Hospitals in Tehran, Iran. Patients meeting the inclusion criteria will be randomly assigned to two groups: one group will undergo LeFort I osteotomy with ANS reduction, and the other group will undergo LeFort I osteotomy without ANS reduction. The soft tissue profile changes, specifically the nasolabial angle and upper lip length, will be evaluated and compared between the two groups.

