### Objective and hypothesis

The major goal of this double arm parallel randomized clinical trial is to see how reducing ANS affects the soft tissue profile after maxillary advancement surgery with an advancement range of 3–5 mm. The null hypothesis is that the changes of nasolabial angle and upper lip length in skeletal class III patients of the study after LeFort 1 osteotomy (maxillary advancement) with and without ANS reduction are not significantly different.

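### Two outcomes share one null hypothesis, neither is primary, the sample size belongs to neither, and no rule says how two results at 0.05 are combined

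*Protocol article*

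**What the plan says.** All references are to the protocol article.

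- **Objective and hypothesis.** There is a single null hypothesis, and it covers two measurements: "The null hypothesis is that the changes of nasolabial angle and upper lip length in skeletal class III patients of the study" are taken not to differ between surgery with and without ANS reduction.
- **Abstract, Method and design.** The same two appear as equals: "specifically the nasolabial angle and upper lip length, will be evaluated and compared between the two groups".
- **Outcomes.** Both are measured before surgery and three months after it: "nasolabial angle and upper lip length will be assessed". Neither is labelled primary or secondary.
- **Sample size.** One repeated-measures ANOVA calculation gives 13 per group. The error rates are in a garbled clause, "0.05 for both within-between subject variables equal to 0.2", best read as α = 0.05 and β = 0.2. The effect sizes are 0.5 for the repeated factor and 0.6 for the between-subject factor. No outcome is attached to either.
- **Statistical analysis.** Groups are compared by "conducting an analysis of variance (ANOVA), considering the type of intervention as a factor", and "The significance threshold is set at 0.05". There is no split of the threshold, no testing order, and no rule for one significant outcome against two.

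The abstract's discussion uses the word primary once, for an objective about the nasolabial region in general. That does not separate the two measurements.

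**The concern.** A joint null hypothesis needs a rule for rejecting it. Without one, the usual course is to test each outcome at 0.05 and to report a difference if either test succeeds. That gives two chances of a false positive, so the joint null is falsely rejected more often than 1 time in 20.

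Two further consequences follow. With no ranking, whichever outcome is significant can become the headline. And because the effect sizes belong to no named outcome, the power of the trial cannot be stated for either one.

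This matters because the Introduction says the trial is to settle which technique is better for 3–5 mm advancements, and the Discussion says the findings will guide treatment decisions. The two outcomes may disagree, and the article gives no way of concluding when they do.

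**Working it through.** **Inputs.** Two outcomes under one null (Objective and hypothesis); threshold 0.05 (Statistical analysis); 13 per group, α = 0.05, β = 0.2, between-subject effect size 0.6 (Sample size). The correlation ρ between the two test statistics is not given, so it is varied.

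**Step 1: the plan's own sample size.** Assume that 0.6 is Cohen's f for a two-group comparison of a single measurement, so that d = 2 × 0.6 = 1.2. With N = 26 the noncentrality is λ = N·f² = 26 × 0.36 = 9.36, on 1 and 24 degrees of freedom. Power at α = 0.05 is 83.5%. With 12 per group it is 80.2%, so 12 would be enough for 80% power. The stated 13 is within one patient per group of that, so the reading is plausible, but the article does not confirm it.

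**Step 2: chance of at least one false positive if either outcome is enough.** With independent statistics it is 1 − (1 − 0.05)² = 1 − 0.9025 = 9.75%. The upper bound at any correlation is 0.05 + 0.05 = 10%. For correlated statistics it is 1 − P(|Z₁| ≤ 1.96 and |Z₂| ≤ 1.96), with Z₁ and Z₂ bivariate normal:

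| ρ | False rejection of the joint null |
|---|---|
| 0 | 9.75% |
| 0.3 | 9.5% |
| 0.5 | 9.1% |
| 0.7 | 8.3% |
| 0.8 | 7.8% |
| 0.9 | 7.0% |

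Simulated t-tests with 13 per group agree: 9.9% at ρ = 0, 8.9% at 0.5 and 7.1% at 0.9.

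**Step 3: other decision rules.** If both outcomes must be significant, the chance of falsely rejecting cannot exceed that of one test, 5%. If one named primary is tested first and the other only after it succeeds, the overall rate is at most 5%. Holm's procedure also holds it to at most 5%.

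**Step 4: what the repairs cost in power.** Under the Step 1 assumption, power per outcome at 13 per group is 83.5% at 0.05 and 74.4% at 0.025. Holm rejects an outcome if its p-value is at most 0.025, or if it is at most 0.05 and the other outcome's is at most 0.025. Its power per outcome therefore lies between those two figures.

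If 0.6 instead describes the average of two measurements with within-patient correlation r, λ is multiplied by 2/(1 + r):

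| r | λ | Power at 0.05 | Power at 0.025 |
|---|---|---|---|
| 0.5 | 9.36 × 1.333 = 12.48 | 92.3% | 86.5% |
| 0.7 | 9.36 × 1.176 = 11.01 | 88.9% | 81.6% |
| 1 | 9.36 | 83.5% | 74.4% |

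The article does not give r.

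**The case against.** The strongest reply has four parts.

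1. **A multiplicity procedure may sit in an analysis plan that is not shown.** This stands, so the absence of such a procedure is not the finding. The finding is what the article does fix: its hypothesis, outcome and sample-size sections are all written without a primary outcome. An analysis plan that ranked the outcomes would have to be reconciled with them.
2. **The either-outcome rule is inferred.** This also stands. The article gives no decision rule. If both outcomes were required, or if each were reported as a separate question with its own 5%, there would be no inflation to report. But neither of those rules is written, and rejection on either outcome is the natural reading of a joint null.
3. **No stated error rate is contradicted.** A reader might infer that the article promises a 5% family-wise rate and breaks it. It does not: 0.05 is given as a significance threshold only.
4. **A headline of 9–10% would be too high.** That range needs a correlation of about 0.5 or less. Both measurements come from the same radiograph, so a higher correlation is possible, and at 0.9 the rate is 7.0%.

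Nothing elsewhere in the article names a primary outcome or links the effect sizes to one.

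**Conclusion.** The point holds in a conditional form. It is established from the text that two outcomes share one null hypothesis on equal terms, that the sample size is tied to neither, and that 0.05 is the only threshold, with no rule for combining the results. If significance on either outcome is taken to reject the hypothesis, the chance of a false rejection is roughly 7–10% for correlations from 0.9 down to 0. It stays above 5% over that whole range.

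Two further inferences are not supported. One is that nasolabial angle must be the primary outcome because it is listed first: order of mention is not a scientific reason, and the choice belongs to the investigators. The other is that protecting the error rate would necessarily take power below 80%. The figure of 74.4% is a floor under one reading of the effect size, and under a repeated-measures reading with within-patient correlation 0.5 or 0.7 power stays above 80% even at 0.025.

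**What to change.** Issue a dated amendment before anyone sees results by group. Recruitment was in progress when the article was submitted, and the statisticians are to be kept unaware of assignments, so this should still be feasible at that stage. The amendment should do two things.

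1. **Choose one structure.**
   - *Fixed order:* name one outcome as primary, tested at 0.05, and test the other at 0.05 only if the first is significant.
   - *Two primaries:* keep both and apply Holm's procedure at 0.05 overall.
2. **Say which outcome the effect sizes of 0.5 and 0.6 describe.** If it is not the outcome chosen as primary, restate the power of 13 per group for the chosen one.

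**Cost.** No patients are added. Under the fixed order, the second outcome cannot be claimed if the first fails. Under Holm, power per outcome falls somewhat: from about 83.5% to no lower than 74.4% if 0.6 is a single-measurement between-group f, and with less loss under the repeated-measures reading. The remaining work is the amendment itself, and a restated power figure if the effect sizes turn out to belong to the other outcome.
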